### Randomization

After the baseline survey is administered, the biostatistician will use SAS (SAS Institute) to perform a permuted stratified blocked randomization [33]. The stratification variable used maintenance therapy versus no maintenance therapy. The rationale for this stratification is that those patients with ovarian cancer who receive maintenance therapy with a poly (ADP-ribose) polymerase (PARP) inhibitor may experience a different symptom burden or illness trajectory that impacts outcomes [3]. Survivors will be randomly allocated to either the control group or the POSTCare intervention group with a 1:1 ratio (N=120). Stratification will be based on disease stage and maintenance therapy (a PARP inhibitor vs Bevicizumab vs no maintenance). Each of these factors is associated with overall QOL and symptom burden. Participants, clinicians, data collectors, biostatisticians, and investigators will be blinded to allocation. The research nurse interventionist (described below) will not be blinded but will not conduct study activities related to measuring, collecting, or interpreting outcomes. Although this is a low-risk intervention, unblinding decisions will be made by the investigators in the context of serious adverse events attributable to the study. If a decision is made to unblind a participant, the study data coordinating center will undertake the unblinding and protect the confidentiality of treatment assignments for other participants. The treatment assignment will be communicated to the participant and the participant’s treating physician. The unblinding event will be reported to the Baylor College of Medicine institutional review board, documented in trial records, and the analysis of study outcomes may be adjusted to account for the unblinded participant to ensure that the integrity of the overall trial results is maintained. Criteria for study dropout include withdrawal of consent, failure to adhere to protocol, loss to follow-up, health changes making further participation burdensome, and personal reasons or changes in life circumstances.

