### Control Group

The control group will receive standard survivorship care delivered through telehealth. All sites have a standard survivorship visit that includes the use of a software package to generate the delivery of a paper SCP based on American Society of Clinical Oncology guidelines. This comprises a treatment summary, an upcoming surveillance visit schedule, and guidance on late effects. This visit includes the delivery of information and specifically does not include goal setting, use of the dual framework technique (described in the “Intervention” section), acceptance and commitment intervention (described in the “Intervention” section), self-management coaching, or the use of motivational interviewing techniques. To ensure fidelity to control group standards, all visits will be audio-recorded and reviewed to evaluate for evidence of contamination of the control condition. Telephone-based booster contacts will serve as attention control with structured delivery of educational material on surveillance visits and bone health.

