### Patient-Centered Design

The POSTCare session begins with the coach engaging the survivor in sharing her cancer treatment narrative, anchoring the activity to the patient’s experience and needs. The identification of health goals is the central activity of POSTCare and distinguishes this approach to survivorship care from those that simply deliver information. The survivor is asked to think about identifying 1 or more goals in the following survivorship domains: social support, healthy habits, symptom management, and coping with uncertainty. Resource and activity support materials related to goals are maintained in the POSTCare-O web-based survivorship toolkit and used by coaches. As an adaptation for the needs of survivors of ovarian cancer, the dual framework [31] is introduced by coaches in goal-setting as a strategy for living with uncertainty. The dual framework is a strategy used in palliative encounters to help patients focus on what living well means to them while holding the possibility of advancing illness or death in the same cognitive frame. It provides a structure to anchor the focus on living well across the longitudinal trajectory of survivorship navigation. We will introduce a brief cognitive exercise derived from acceptance and commitment therapy to address recurrence worry if participants articulate this as a survivorship concern and goal [22,36-38]. Our informants indicated that using a focus on what it means to live well despite serious illness is an acceptable palliative intervention even at the initiation of the survivorship period when they wish to be focused on the positive aspects of treatment completion.

The coach and survivor strategize about potential barriers to goal accomplishment and explore ways to address barriers, with the coach using motivational interviewing techniques to explore survivor ambiguity about health goals and nurture self-efficacy in working toward goals. The components of the platform, drawn from an evidence-based approach to care setting transition [24,25,27,39-41], include an emphasis on survivor engagement and activation. The average length of the coaching session is 75 minutes, which includes the creation of the SCP [21].

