### Qualitative Methods

Qualitative methods will be used to inform the adaptation and refinement of the intervention. Interviews will be undertaken with 3 groups of informants: women living with ovarian cancer; nurses who have been trained in the POSTCare model; and gynecologic oncologists, clinic staff, and administrators. Semistructured exit interviews will be conducted by specially trained research team members within 30 days of completing the intervention. Although the exit interview questions will be stated as broad questions, the researcher will be trained to probe for details, including asking for specifics and operational examples.

We will partner with women enrolled in this study to conduct semistructured interviews on the POSTCare survivorship care experience. Interview topics will include (1) timing of survivorship care—both initiation of survivorship transition and longitudinal care; (2) critique of proposed intervention content and existing materials; (3) understanding the meaning of this intervention for participants; (4) exploring individual differences between experiences and outcomes; and (5) evaluation of intervention length, intensity, frequency, and mode of delivery. Interviews will be conducted with gynecologic oncology nurses who have completed the POSTCare-O web-based training and used components of the POSTCare model to provide the intervention. Finally, we will explore the same interview topics with clinic staff at each study site to learn what elements of the POSTCare model work well in their clinical setting, which elements they are able to use routinely, which components seem to most meet the needs of their patients, and which elements of survivorship care they find most satisfying.

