## Discussion

### Overview

The overarching goal of this research program is to improve QOL and well-being for women living with ovarian cancer. This paper details the protocol for a randomized, controlled, dual-blinded study testing a survivorship care platform for women completing initial treatment for ovarian cancer. The gaps in science related to the care of patients with advanced or incurable cancer are thoughtfully articulated in a recent National Cancer Institute meeting report [6].

This study will address several of the gaps in science that exist relative to women living with ovarian cancer. Much of the science focused on the needs of survivors of cancer has been conducted in breast cancer populations; however, a solid body of work exists that characterizes the impact of ovarian cancer and treatment on QOL, sexual well-being, care preferences, and health care use. This study, with a collection of measures related to symptom burden and psychosocial well-being, will characterize unmet needs at baseline among survivors of ovarian cancer, and we will be able to place our work in the context of the existing science for interpretation. Further, our qualitative stream will provide additional context for interpretation of our quantitative data as we work to better understand the patients’ experience.

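### Participants and biostatisticians are called blinded although the design as described does not blind them, and two related rules (adjustment after unblinding, timing of exit interviews) need tightening

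*Protocol article*

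**What the plan says.** Blinding. The Randomization section of the protocol article states: "Participants, clinicians, data collectors, biostatisticians, and investigators will be blinded to allocation". It excepts only the research nurse interventionist, who is kept away from measuring, collecting and interpreting outcomes. The Overview of the Discussion describes a "randomized, controlled, dual-blinded study".

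Who randomises. Earlier in the same Randomization section, once the baseline survey is done, "the biostatistician will use SAS (SAS Institute) to perform a permuted stratified blocked randomization".

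What the arms receive. On the control visit, the Control Group section says: "This visit includes the delivery of information and specifically does not include goal setting". It also rules out coaching and motivational interviewing. For POSTCare, the Patient-Centered Design section makes identifying health goals the central activity and adds: "The average length of the coaching session is 75 minutes". Both arms are delivered by telehealth, and the control arm has telephone boosters that serve as attention control.

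Outcome source. Table 1 gives patient self-report as the source for FACT-O.

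After unblinding. If a woman is unblinded following a serious adverse event attributed to the study, "the analysis of study outcomes may be adjusted to account for the unblinded participant".

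Interviews. The Qualitative Methods section says: "Semistructured exit interviews will be conducted by specially trained research team members within 30 days of completing the intervention". The interviews with enrolled women concern their experience of POSTCare.

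**The concern.** Blinding of participants matters most when the participant is also the outcome assessor, as with FACT-O. A woman who has set goals and been coached knows what she received. If the report says participants were blinded, readers will discount expectation effects that the design leaves open.

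The biostatistician statement is a contradiction in the text: one role both performs the allocation and is listed as blinded to it, and the article describes nothing that separates the two tasks.

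Two neighbouring rules have a similar weakness. The unblinding clause lets the outcome analysis change after a post-randomisation event that the investigators judge, with no method or limit. The interview window can place an extra, reflective contact about POSTCare shortly before the primary self-report for the women interviewed.

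**Working it through.** There is no figure in the plan to reproduce for the blinding claim itself. The check compares the text by role, then does day arithmetic for the interviews, then gives one illustration of size.

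**1. Roles listed as blinded, against the described procedures**

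- Participants: the visits differ in content by design (Control Group; Intervention; Patient-Centered Design). Allocation is evident from the care received, at least in the sense of which kind of care it was. The claim is not supported.
- Biostatisticians: one performs the randomisation; no second statistician or masked coding is described. The claim is contradicted as written.
- Clinicians: the article does not say who delivers the control visit, and treating clinicians need not know each woman's arm. Uncertain.
- Data collectors: the baseline survey is web-based and self-administered, so blinding is feasible. Not disputed.
- Research nurse: already declared unblinded. No conflict.

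**2. Interview window against the primary survey**

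Inputs: boosters at weeks 4 and 8 after baseline (Patient-Centered Design), so the last is on day 8 × 7 = 56. The interview window is 30 days, so days 57 to 86. The survey is at 12 weeks, and the article gives three different starting points for those weeks:

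- From the survivorship transition (Study Design), taken as about baseline: survey on day 12 × 7 = 84. Days 57 to 83 precede it, that is 27 of the 30 window days.
- After the intervention (Abstract, Results): survey on about day 56 + 84 = 140. The whole window precedes it.
- After initial adjuvant chemotherapy (Sample Size; Outcome Measures): survey on study day 84 − L, where L is the lag in days from the end of chemotherapy to baseline. The intervention ends before the survey only if 84 − L > 56, that is L < 28. With a longer lag the survey comes first.

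If the optional phone check-in before the 3-month visit (Intervention) counts as the end of the intervention, the window opens later than day 57.

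**3. Illustration of expectation bias**

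Assumptions: two-sided 5% test (the article states neither alpha nor sidedness), and 80% power at the stated 8-point difference. Then

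SE = 8 / (1.96 + 0.84) = 2.86 points.

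With no true effect and a bias b in the POSTCare arm mean, the false-positive rate is Φ(b/SE − 1.96) + Φ(−b/SE − 1.96):

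- b = 2: b/SE = 0.70, rate = 0.108
- b = 3: b/SE = 1.05, rate = 0.183

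Both values of b are assumed. They lie at or below the lower end of the 3 to 8 point minimally important difference given under Outcome Measures.

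**4. Why the illustration cannot be carried over to the interviews**

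Up to 30 interviews are anticipated, and informants fall into three groups: women, nurses, and oncologists with clinic staff and administrators. If all 30 were among the 60 POSTCare women, an arm-mean shift of 2 to 3 points would need 2 × 60/30 = 4 to 3 × 60/30 = 6 points per interviewed woman. If 10 were (assumed), it would need 2 × 60/10 = 12 to 3 × 60/10 = 18 points.

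**The case against.** The design has real safeguards. Both arms have a telehealth survivorship visit, a care plan and booster calls, so a woman may know what she received without knowing which arm is experimental. The consent text is not shown. The nurse is openly unblinded and kept away from outcomes. This stands as mitigation, but being unaware of the hypothesis is a weaker property than being blinded to allocation, which is what the article claims.

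On the biostatistician, generating a list and analysing under masked codes are compatible, and the data coordinating center handles unblinding and protects the other assignments. A reader might infer that a blinded analysis is impossible; the text does not show that. What stands is that the article assigns both properties to one role without saying how they are kept apart.

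On the adjustment clause, a reader might infer that unblinded women would be dropped. The clause does not mention exclusion, and its trigger should be rare in a study the article calls low-risk. What stands is that it permits a discretionary change linked to a post-randomisation event.

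On the interviews, the overlap depends on an unreconciled starting point for the 12 weeks and on what counts as the end of the intervention, and only a subset is interviewed. All of that stands. It makes the point minor, but nothing in the article requires the survey to come first.

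**Conclusion.** The blinding statement should be corrected for participants and clarified for biostatisticians; the dual-blinded label is not supported by the described design. This rests on the article's own account of the visits, the self-reported primary outcome and the randomisation procedure, and needs no assumption about bias.

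The size of any bias is unknown. The rise in the false-positive rate from 5% to about 11-18% is an illustration under an assumed SE of 2.86 and an assumed bias of 2 to 3 points. It applies to expectation bias in the arm mean and takes no account of the attention control. It should not be read as an effect of the interviews or of the adjustment clause, for which no size can be given.

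A reader might also infer that all listed roles are in fact unblinded. The documents do not support this: data collectors can be blinded, and whether treating clinicians know the arm is uncertain.

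The adjustment clause and the interview timing are secondary but cheap to correct. The interview point holds as a possibility: 27 of 30 window days precede the survey if both are counted from about baseline and the week-8 booster ends the intervention.

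**What to change.** - Delete the dual-blinded label and take participants off the blinded list. At most, describe them as unaware of the study hypothesis, if the consent text supports that.
- State that data collectors and the analysing statistician are blinded, and have the allocation list generated and held separately, for example by the data coordinating center. Say who delivers the control visit and word the claim about clinicians to match.
- Replace the adjustment clause with a primary analysis of all women as randomised; allow any adjustment for unblinding only as a prespecified sensitivity analysis.
- Reconcile the starting point of the 12 weeks, and hold participant exit interviews after the 12-week survey is complete.

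The cost is rewording, a transfer of list generation to a separate holder, and slightly longer recall in the participant interviews. Sample size, outcome measures and the content of care do not change.

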Few studies have examined the impact of survivorship care plans (SCPs) for survivors of ovarian cancer on their QOL. The Registration System Oncological Gynecology trial was a pragmatic cluster randomized trial in which 12 hospitals were randomized to deliver computer-generated SCPs or usual care. The SCP was based on a Dutch translation of the Institute of Medicine format [7]. A total of 174 patients with ovarian cancer enrolled in the trial, of whom 61 received care at an SCP hospital and 113 received care at a usual care hospital. The primary analysis outcomes included satisfaction with care, illness perception, and health care use. There were no overall effects of SCP delivery on any of the scales of satisfaction with care; at 12 months of intention to treat (ITT) analysis, patients in the SCP arm rated the interpersonal skills of nurses lower than patients in the usual care arm. Patients in the SCP arm experienced more symptoms, were more concerned about their illness, and were more emotionally affected than patients in the usual care arm [17]. Further analyses showed increases in health care use among women with anxiety symptoms and those who received radiotherapy [18,19]. Investigators found that patients with ovarian cancer who had lower trust that the treatment would cure their disease due to the SCP reported worse emotional functioning 6 months after treatment [20]. Taken in total, the Registration System Oncological Gynecology trial underscores that for women with ovarian cancer, a templated SCP that emphasizes the frightening long-term outcomes of this disease may impair outcomes. In response to this study and the concerns of our patients, we engaged patients with ovarian cancer and providers to provide input on the development of POSTCare-O. Their input resulted in a goal related to living well with a serious illness and the inclusion of specific strategies to cope with recurrence anxiety.

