Other measures used as secondary outcomes and potential predictors were selected with a priority on acceptable psychometric performance in similar populations and acceptable performance in one of our previous studies.

“Aim 1” proposes to implement a RCT devised to compare QOL measures among patients with ovarian cancer randomized to receive usual care versus the POSTCare survivorship care transition program. Outcome measures, including the FACT-O QOL survey, the FCR-7 survey, and the PHQ-9, will be collected at baseline as well as 12 and 24 weeks after the initial course of adjuvant chemotherapy. The primary end point will consist of the 12-week FACT-O survey. The sample size of 120 patients provides at least 80% power to detect a 7% increase in the mean FACT-O score for women randomized to the POSTCare survivorship care intervention. This is sufficient to ascertain a minimally important difference of 8 points. Secondary outcomes (Table 1) will also be assessed at 12 and 24 weeks. Baseline descriptive statistics will be presented by site. Longitudinal analysis of the FACT-O QOL scores will use a mixed effects linear model with a restricted maximum likelihood estimation method, and an unstructured covariance matrix will be used to estimate trends. An interaction between intervention and time will be estimated to explore the effectiveness of POSTCare for time-varying trends [49]. Though the mixed effect model can accommodate some degree of missing data under the ignorability assumption, we also plan to use multiple imputations using the random forest method [50,51] to accommodate missing data (if greater than 10% of survey items), which will be assumed to be missing at random. In the event of a sign of a violation of that assumption, a pattern mixture model will be used to mitigate the effect of informative missingness. Secondary analyses will evaluate relationships between baseline and 12-week FACT-O scores and clinical end points progression-free survival (PFS) and overall survival (OS). Cox proportional hazard models will be used to estimate the relative risk of PFS and death per increase in FACT-O [52]. Ties in failure times will be handled with the approximate likelihood of Efron. PFS and OS will be measured from the date of randomization. PFS is defined as the minimum amount of time until clinical progression, death, or the date of last contact. OS is the duration from randomization to death or to the date of last contact (right-censoring). As is customary, secondary analyses are not powered but may help generate additional evidence that needs to be tested in the future by a properly powered study.

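### Non-adherence is listed as a reason to leave the study, and the only analysis that drops missing at random waits for an undefined sign that the data cannot give, so the 12-week contrast is exposed to informative dropout of unknown direction and size

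*Protocol article*

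**What the plan says.** The Randomization section of the protocol article ends with a list: "Criteria for study dropout include withdrawal of consent, failure to adhere to protocol, loss to follow-up, health changes making further participation burdensome", followed by personal reasons or changed circumstances. The list concerns leaving the study. Nothing in it distinguishes a woman who stops engaging with her assigned care from one who stops giving outcome data.

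Under Outcome Measures, "The primary end point will consist of the 12-week FACT-O survey". On the model, "Longitudinal analysis of the FACT-O QOL scores will use a mixed effects linear model with a restricted maximum likelihood estimation method", with an unstructured covariance matrix. On missing data, the article begins "Though the mixed effect model can accommodate some degree of missing data under the ignorability assumption" and adds multiple imputation by random forest "to accommodate missing data (if greater than 10% of survey items), which will be assumed to be missing at random". The only departure from that assumption is conditional: "In the event of a sign of a violation of that assumption, a pattern mixture model will be used". The article does not say what would count as such a sign.

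**The concern.** Two stated rules act on the same outcome, one after the other.

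The first can generate missing data that need not be missing. A woman who misses coaching contacts can still fill in a questionnaire. If she is treated as having left the study, her 12-week score is lost because of something that happened after randomisation and that her assigned arm may have influenced. The arms differ in what they ask: POSTCare has goal setting, self-management coaching and a session averaging 75 minutes, while the control visit delivers information.

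The second rule decides how that loss is handled. Non-adherence and burdensome health changes are plausibly related to quality of life, yet the default treats the loss as ignorable, and the analysis that relaxes this depends on a trigger that cannot do its job. It may never be run, or it may be run by choice once the data are known. What is at stake is whether the 12-week FACT-O difference still compares the groups that were randomised.

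**Working it through.** **Step 1. Which listed reasons must end data collection?** Loss to follow-up does by definition, and withdrawal of consent usually does. Non-adherence does not: FACT-O is patient self-report (Table 1), and Recruitment Procedures describes a web-based, self-administered baseline survey. The missing scores this item can produce are therefore avoidable.

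**Step 2. Can the data give the sign?** Let Y be the 12-week FACT-O and X the observed data (arm, baseline, other visits). Missing at random says that Y given X has the same distribution in women whose Y is seen and in those whose Y is not. The second distribution is never observed. Let k be the amount by which unseen scores fall below the missing-at-random prediction. Then k = 0 and k = 8 fit the same observed data equally well. Unequal dropout between arms is compatible with missing at random, and equal dropout is compatible with its failure. Recorded reasons can make a violation plausible but cannot establish or exclude it.

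**Step 3. Inputs for size.**
- From the article: 60 per arm, an 8-point target difference, at least 80% power.
- Not stated: SD, alpha, dropout rate. I assume two-sided alpha of 0.05. The stated power then needs an SD of at most 8 / [√(2/60) × (1.960 + 0.842)] = 15.64. I use that value. The power figure is only solved backwards here, not confirmed.
- Assumed: dropout shares p1 and p0, and shortfalls k1 and k0, all varied.

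**Step 4. Formulas.** Bias b = p1·k1 − p0·k0. SE = 15.64 × √(1/n1 + 1/n0), where n = 60(1 − p). Type I error = Φ(b/SE − 1.96) + Φ(−b/SE − 1.96). The SE is that of a simple two-group comparison, a simplification of the planned mixed model.

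Worked case, 20% v 10% with k = 8 in both arms: b = 0.20×8 − 0.10×8 = 0.8 points, and 0.8/8 = 10% of target. SE = 15.64 × √(1/48 + 1/54) = 3.10, so b/SE = 0.26 and type I error is 5.8%.

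| Dropout, arm 1 v arm 0 | Shortfall, arm 1 v arm 0 | Bias (points) | Share of 8 | Type I error |
|---|---|---|---|---|
| 20% v 20% | 8 v 8 | 0 | 0% | 5.0% |
| 20% v 10% | 4 v 4 | 0.4 | 5% | 5.2% |
| 20% v 10% | 8 v 8 | 0.8 | 10% | 5.8% |
| 30% v 10% | 8 v 8 | 1.6 | 20% | 7.9% |
| 30% v 10% | 15.64 v 15.64 (1 SD) | 3.13 | 39% | 16.3% |
| 20% v 20% | 15.64 v 0 | 3.13 | 39% | 16.5% |

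The bias raises the apparent mean of arm 1, which could be either arm.

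**Step 5. What baseline recovers.** The shortfall k is measured against the missing-at-random prediction, not against the women who stay. Suppose instead that 8 points is the whole gap between leavers and stayers, that it is already present at baseline, that SDs are equal, and that baseline and week 12 correlate at r. A model using baseline then leaves 8 × (1 − r). For 20% v 10% the bias falls from 0.8 to 0.10 × 8 × 0.5 = 0.4 points at r = 0.5, and to 0.10 × 8 × 0.2 = 0.16 points at r = 0.8.

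**The case against.** A reader might infer that non-adherers are removed from POSTCare, that their 12-week survey is not taken, and that the result is tilted in favour of POSTCare. The documents do not support that much. The list mixes rules staff could apply with reasons women simply leave, so it may be descriptive. Adherence is not defined and could include completing surveys. No sentence says the survey stops or that anyone is excluded from analysis. The Control Group section gives controls telephone boosters as attention control, so booster calls are not an extra demand on one arm, and no control visit length is given for comparison with 75 minutes. Health changes are a reason in both arms. All of this stands: differential loss is possible but not shown, and so is its direction.

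It is also fair that a mixed model with baseline FACT-O recovers part of any deficit, so multiplying the dropout share by the raw gap overstates the bias (Step 5). The large type I errors need 1-SD shortfalls with very unequal dropout, or with the shortfall in one arm only.

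Two further inferences should be resisted. Intention to treat is named in the text only for an earlier trial ("at 12 months of intention to treat (ITT) analysis, patients in the SCP arm rated the interpersonal skills of nurses lower"), but silence in a condensed article is not evidence that this trial will not analyse as randomised. The clause that "the analysis of study outcomes may be adjusted to account for the unblinded participant" is loosely worded, but it concerns unblinding in the context of serious adverse events in what the article calls a low-risk intervention; it does not speak of exclusion, and its effect cannot be sized.

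Finally, a pattern mixture model is planned, and its details may sit in an analysis plan that is not shown. That answers any charge that the analysis is absent. It does not answer the trigger, which the article itself states, and a plan that followed it would carry the same fault.

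**Conclusion.** The point holds as a risk built into two stated rules, not as a demonstrated bias. Non-adherence as a study dropout criterion can cause avoidable, post-randomisation loss of the primary outcome. Making the analysis outside missing at random depend on a sign leaves it without a workable rule. Direction and size are unknown. With 20% v 10% dropout and an 8-point shortfall the bias is 0.8 points, 10% of the target, with type I error near 5.8%. It is smaller if baseline predicts part of the deficit, and zero if dropout and shortfall match between arms. These figures rest on assumed dropout, shortfall, SD (15.64) and alpha. A claim that the trial will favour POSTCare, or that the randomised comparison is already broken, goes beyond the text.

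**What to change.** 1. Remove non-adherence from the study dropout criteria, and separate stopping the assigned care from leaving follow-up.
2. State that women who stop or do not adhere stay on the 12- and 24-week surveys unless they decline, and are analysed in the arm to which they were randomised.
3. Replace the conditional trigger: run the pattern mixture analysis unconditionally, as a prespecified delta-adjusted sensitivity analysis of the 12-week FACT-O contrast, with the shortfall allowed to differ between arms.

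The cost is protocol wording, continued web surveys for non-adherers and one extra table. The estimate may be slightly less favourable if non-adherers do worse. The first two changes matter most while follow-up is running, since scores that were never collected cannot be recovered at analysis.
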